#### Parent-child interactions, child behavioral and emotional functioning

**Coding interactive behavior (CIB)** is a clinician-rated measure coding adult-child interactions applicable for children from the newborn stage and up to adolescence [40]. In the current trial we are using the preschooler version. Video sequences of several parent child interactions are observed and coded on a 5-point Likert scale by a blinded rater, where 1 implies a minimal level of a specific behavior or attitude and 5 implies the maximal level. The parent child interactions are filmed during free play, structured play (puzzle) and a child-frustrating task. Coding of these situations is focused on the global nature, flow of the session and the interactive involvement of child and parent.

The coding scheme for the preschooler version consists of 44 scales; 22 scales regarding the adult behavior (like e.g. acknowledging, intrusiveness-overriding, hostility, praising) 15 scales regarding the child behavior (like e.g. child positive affect, withdrawal and compliance to parent), and 7 dyadic scales regarding the interaction between child and parent (like e.g. dyadic reciprocity, adaptation-regulation). These different scales are condensed into eight composite scores regarding the a) *parent*: 1) sensitivity, 2) intrusiveness and 3) limit setting; b) *child*: 4) involvement, 5) withdrawal and 6) compliance and c) *the dyad*: 7) dyadic reciprocity and 8) dyadic negative states. The CIB has shown good psychometric properties [40]. CIB has been used in a number of studies and has shown adequate construct and predictive validity, as well as test–retest reliability [41–44].

**Child Behavior Check List (CBCL) or CBCL/11/5-5** is also called the *Achenbach System of Empirically Based Assessment (ASEBA)* [45]. The CBCL is a parent-reported questionnaire screening for emotional, behavioral, and social problems of the child. Two different versions of the CBCL exist depending of the age of the child: a) the preschool version (age 1,5–5 years); and b) the school -aged child version (age 6–16 years). The CBCL has a total score and two indexes: *internalizing and externalizing* symptoms. The CBCL also contains specific subscales associated with disorders from the *Diagnostic and Statistical Manual of Mental Disorders* [46]: anxiety, oppositional defiant disorder, conduct problems, somatic problems, affective problems, and attention deficit disorder. A high rate of reliability between the scales of the CBCL and actual psychiatric diagnoses has been shown [47].

**Berkeley Puppet interview (BPI)** [48, 49] is a semi-structured interactive interview for children. The interviewer uses two hand puppets providing contradictory statements (“I’m a happy child” and “I’m not a happy child” “What about you?”) to gain access to the children’s perspective regarding their own emotional and behavioral problems, peer acceptance, social functioning and parent-child relationship. The child interview is videotaped and rated by blinded raters. The BPI has shown acceptable psychometric properties [49, 50].

**Parent-rated Eyberg Child Behavior Inventory (ECBI)** [51] is a 36-item parent-reported questionnaire about the behavior of their child (age 2–16 years). Each question asks how frequently a specific behavior occurs *and* if the behavior is a problem for the parent. ECBI is both used in clinical practice and intervention studies and contains two subscales: 1) the *Intensity subscale* measures how frequently each behavior occurs rated on a 7-point Likert-type scale and 2) the *Problem subscale* contains all the previously rated questions, but it is rated as a yes–no response about the parent considering the child’s behavior to be problematic. ECBI has good internal consistency, with alpha values for the Intensity and Problem Scale 0.93 and 0.91 [52], respectively and it is sensitive to detect intervention effects [53].

**Parent-rated Strengths and Difficulties Questionnaire (SDQ)** [54] is a 25-item questionnaire about strengths and weaknesses of the child. Additionally there is one impact question about whether the parent thinks that the child has a problem. If that is the case, then chronicity, distress, social impairment, and burden to others are also addressed. SDQ results in a total difficulties score, including four subscales regarding emotional symptoms, conduct problems, hyperactivity, and peer problems. Additionally, there is a prosocial behavior subscale. The Danish version of the SDQ has been found to have acceptable psychometric properties [55, 56].

**Attention Deficit Hyperactivity Disorder-Rating Scale (ADHD-RS) or Pre-school ADHD-RS** [57] is a parent rating scale of ADHD symptoms. The Danish version consists of 26 questions, including oppositional behavior questions, all rated on a 3-point Likert scale. ADHD-RS consists of 3 subscales: inattention, hyperactivity and oppositional behavior subscale [58]. ADHD-RS has shown to be valid and clinically feasible in a Danish population [57].

#### Parents reflective functioning and parenting experiences

The following questionnaires are self-reports of parents about their own perceptions and symptoms:

**The Coping with Children’s Negative Emotions Scale (CCNES)** [59] is a self-report measure for parents on how they would likely respond in 12 imaginary situations, in which their child is distressed. For example “If my child becomes angry because he/she is sick or hurt and can’t go to his/her friend’s birthday party, I would..” and the parent can then choose between 6 options for each of the 12 questions. Questions are rated on a 7-point Likert scale from 1 = very unlikely to 7 = very likely. Coping with Children’s negative emotions is a valid and reliable measure [59] and it results in six parent reaction patterns: 1) emotion focused, 2) problem-focused, 3) minimization, 4) punitive, 5) expressive encouragement, and 6) distress coping reaction pattern. CCNES has shown good reliability and validity [59].

**Parental Reflective Functioning Questionnaire (PRFQ)** (short 18 item version) measures levels of parental mentalization understood as the capacity of the parent to reflect on and understand the mental states and internal motivation of one’s self and their child. Mentalization is about being able to understand that feelings, beliefs and goals play an essential role in the well-being and development of the child. PRFQ consists of 18 items and results in three categories:1) Pre-Mentalizing modes 2) Certainty about mental states and 3) Interest and curiosity about mental states. The PRFQ has shown preliminary satisfactory validity and reliability [60–62].

**Parental Stress Scale (PSS)** [63] is measuring the level of stress the parents experience in raising a child. The PSS consists of 18 items depicting positive and negative themes of parenthood. The items are rated on a 5-point Likert scale ranging from 1 =“strongly disagree” to 5 =“strongly agree” and result in an overall score, that can range between 18–90. Higher scores indicate greater stress. PSS has satisfactory levels of internal reliability (0.83), and test-retest reliability (0.81) [63].

#### Parental psychopathology and attachment

In order to investigate possible mediators and moderators of treatment, we are also measuring symptoms and attachment quality of the parents with the following scales:

**Standardized Assessment of Personality-Abbreviated Scale, (SAPAS)** [64] is an screening questionnaire for personality disorder/ dysfunction with only 8 yes/ no questions. Although the scale is very brief, a score of 3 positive responses or more is associated with a personality disorder. SAPAS can correctly identify 90% of patients with a DSM-IV personality disorder. Its sensitivity (0.94) and specificity (0.85) are satisfactory [64].

**Brief Symptom Inventory (BSI)** Is a short 18-item version of the SCL-90-R instrument Symptom Checklist-90 (SCL-90) [65]. The BSI-18 [66] screens for psychiatric disorders and psychological distress and has three 6-item subscales: somatization, depression, and anxiety. The BSI has shown to be a reliable instrument for the assessment of psychological distress with good psychometric properties [67].

**Major Depression Inventory (MDI)** [67] is a 12-item self-report depression questionnaire developed by the World Health Organization. It is used to estimate depression symptom severity in the last 2 weeks and is based both on the DSM-IV symptoms of major depression and the ICD-10 symptoms of moderate to severe depression. The MDI has shown acceptable psychometric properties [68].

**Revised Adult Attachment Scale (RAAS)** [69, 70] is an 18-item scale assessing three adult attachment dimensions: 1) *Close*: comfort with intimacy, 2) *Depend*: ability to depend on others and 3) *Anxiety*: about being rejected or unloved. It is rated on a 5-point Likert scale ranging from 1 (not at all characteristic of me) to 5 (very characteristic of me). In a sample of undergraduates, Cronbach’s alphas for the close, depend, and anxiety subscales were .77, .78, and .85, respectively [69].

An overview of the progress through the different phases of the current trial can be found in Fig 2.

**Fig 2 pone.0265676.g002:**
[figure not shown]
CONSORT flow diagram. Flowchart of the different phases of the COS-P trial.

### Outcomes

#### Primary outcome

The primary outcome in our trial is parental sensitivity of the mother (or primary caretaker) as measured with the Coding Interactive Behavior (CIB). Parental sensitivity is a composite score consisting of the following subscales: Acknowledging, Elaborating, Parent Gaze/Joint Attention, Positive Affect, Vocal Appropriateness, Appropriate Range of Affect, Resourcefulness, Praising, Affectionate Touch, Parent Supportive Presence.

#### Secondary outcome measures

All secondary outcomes are measured at baseline, at follow-up after the intervention period, and at 6 months follow up.

Maternal Intrusiveness: Measured by observing mother-child interactions and is rated using "Coding Interactive Behavior" (CIB)Limit Setting (CIB)Dyadic reciprocity (CIB)Negative states (CIB)Child Behaviour Check List (CBCL)-externalized symptomsCBCL-internalized symptomsEyberg Child Behaviour Inventory (ECBI) Parent questionnaire on child behaviourBerkeley Puppet Child interviewCoping with children’s negative emotions scaleParenting Stress ScaleSDQ

### Exploratory outcomes

Parental Reflective Functioning QuestionnaireADHD-RS: Parent questionnaire on child ADHD symptomsCoding Interactive BehaviorChild Behaviour Check ListMajor Depression Inventory: Parent questionnaire on their own depressive symptomsRevised Adult Attachment Scale (RAAS): Questionnaire regarding the attachment style of the parent at baselineStandardized Assessment of Personality (SAPAS) -parent: at baselineBrief Symptom Inventory (BSI)

### Risks and side effects

The COS-P intervention has been used extensively in Europe, USA and Australia and translated into eight languages. No associated risks have been reported in previous trials and the intervention is not assumed to have negative effects. Patients’ TAU will not be affected by the participation in this trial.

The participating children, who are on medication are required to be on a 4 weeks stable medical treatment. Families will be asked not to initiate or change the child’s medication during the trial period of 10 weeks, Nevertheless, if the change in medication is necessary, the final decision will be made by parents and the treating physician, who is unrelated to the trial. Possible changes in medication status during the trial will be registered at all assessment points.

### Discontinuation and withdrawal

Enrolled families can withdraw from the trial without further explanation at any point. If a child or a parent requires more intensive care as inpatient hospitalization, the participant can be exited from the trial.

To promote retention and completion of follow-up, children will receive gift cards worth total of 400 DKK. If participants decide to leave the trial earlier, they will receive gift cards for the attended assessment sessions. Transportation costs will be reimbursed for all meetings.

## Statistical plan and data analysis

### Sample size and power analysis

We are planning a trial of a continuous response variable Coding Interactive Behavior from independent control and experimental participants allocated at a 2:1 ratio.

Based on a meta-analysis of attachment-based interventions [71] we expect a standardized effect size of *d* = 0.44 for comparing the change in maternal sensitivity from baseline to follow-up between the intervention group and the control group. Using significance level of 5% and power of 80%, and with a 2:1 randomization ratio, 124 participants in the intervention group and 62 in the control group are needed (total *N* = 186).

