#### Intervention group

In addition to TAU that children in both groups receive, parents of children in the intervention group will participate in 10 manualized COS-P sessions. Although the original COS-P consists of 8 sessions, we choose to add two more sessions allowing more time for in depth discussion. Each of the sessions have a 2-hour duration and are conducted at the clinic by two COS-P-certified therapists. Treatment groups consist of 4–5 families. If parents miss a session, they are offered an 30-minutes make-up session.

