#### Randomization

In this parallel superiority randomized controlled trial participants are randomized 2:1 to the intervention group or control group in a web based randomization system. The allocation sequence is computer-generated with a varying block size kept unknown to the investigators. The allocation sequence has been set up by an independent statistician, who is not involved in the trial. Participants are screened for eligibility by research assistants and given an unique ID number. If all eligibility criteria are met, then the randomization is performed in a web based system and is stratified for site. Research staff has no access to the allocation sequence. Research assistants are informing families about their allocation and participation in the trial.

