### Analytical model

For the intent to treat analysis of the primary, secondary and explorative outcomes, regression analysis and /or ANOVA will be used. For not normally distributed data, robust standard errors, truncation or transformation will be used. For missing data, the direct maximum likelihood method (full information likelihood) or multiple imputations will be used. In addition, per protocol analyses will be conducted for patients completing at least seven sessions, using regression analysis and /or ANOVA with robust standard errors, truncation or transformation when needed.

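### The sample size of 186 makes no allowance for COS-P being delivered in groups of 4–5 families in one arm only, and the analysis section does not account for that grouping

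*Protocol article*

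**What the plan says.** All references are to the protocol article.

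- *Sample size and power analysis* plans for a continuous response "from independent control and experimental participants allocated at a 2:1 ratio". It continues: "we expect a standardized effect size of *d* = 0.44", for the between-arm comparison of change in maternal sensitivity. At 5% significance and 80% power this leads to 124 intervention and 62 control families, 186 in total. No ICC, design effect or inflation factor appears.
- *Intervention group*: "Treatment groups consist of 4–5 families". There are ten two-hour sessions, each led by two certified therapists. *Circle of security* describes reflection and discussion among the parents in the group as part of how the programme works.
- *Control group*: these families receive treatment as usual, and the trial forms no groups among them.
- *Analytical model*: for all outcomes, "regression analysis and /or ANOVA will be used". Robust standard errors are listed together with truncation and transformation as remedies for non-normal data. Neither treatment group nor therapist is mentioned.

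**The concern.** Families in the same COS-P group share therapists, sessions and discussion, so their outcomes may be more alike than those of families in different groups. Controls have no such structure. The design is therefore partially nested: about 25 to 31 clusters in the intervention arm (124/5 = 24.8; 124/4 = 31) and individuals in the control arm.

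With positive within-group correlation, the intervention mean is less precise than 124 independent observations would make it. One of two things then follows. Either the analysis accounts for the groups and has less power than stated, or it ignores them and the p-value is too small and the confidence interval too narrow. The primary comparison of maternal sensitivity is exposed to this, and so are the other outcomes.

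**Working it through.** **Inputs from the article.** d = 0.44 (SD taken as 1); significance level 5%; power 80%; 124 versus 62; group size 4–5. Sidedness is not stated. A two-sided test is inferred, because a one-sided test would need only 48 controls (N = 144).

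**Assumed inputs.** The ICC is not given, so 0.02 to 0.20 is shown. Mean group size m = 4.5, hence k = 124/4.5 = 27.6 groups. Total variance is equal in both arms.

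**Step 1: reproduce 186.** The normal approximation gives n(control) = 1.5 × ((1.96 + 0.8416)/0.44)² = 60.8, so 61 controls and N = 183. With the noncentral t, 61 + 122 gives power 0.797 and 62 + 124 gives 0.803. So 186 is the smallest exact 2:1 split reaching 80% under independence, with almost no slack.

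**Step 2: put clustering in the COS-P arm only.**

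- Design effect: DE = 1 + (m − 1) × ICC
- Standard error: SE = √(1/62 + DE/124); the naive value (DE = 1) is 0.1555
- Power: noncentral t with noncentrality 0.44/SE and Satterthwaite degrees of freedom, taking groups as the units in the COS-P arm
- Two-sided type I error of a test using the naive SE: 2 × [1 − Φ(1.96 × 0.1555/SE)]

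Worked case, ICC 0.10:

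- DE = 1 + 3.5 × 0.10 = 1.35
- Variance components: 1/62 = 0.01613 and 1.35/124 = 0.01089; SE = √0.02702 = 0.1644
- df = 0.02702² / (0.01613²/61 + 0.01089²/26.6), about 84
- Noncentrality 0.44/0.1644 = 2.68; power 0.754
- Type I error 2 × [1 − Φ(1.96 × 0.1555/0.1644)] = 6.4%

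| ICC | DE | SE | SE / naive SE | Power, groups accounted for | Type I error, groups ignored |
|---|---|---|---|---|---|
| 0.02 | 1.07 | 0.1573 | 1.012 | 0.79 | 5.3% |
| 0.05 | 1.175 | 0.1600 | 1.029 | 0.78 | 5.7% |
| 0.10 | 1.35 | 0.1644 | 1.057 | 0.75 | 6.4% |
| 0.20 | 1.70 | 0.1727 | 1.111 | 0.71 | 7.8% |

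A simulation of 20,000 runs, with an ordinary t-test and groups of 4–5, gave type I error of 0.050, 0.057, 0.064 and 0.080 at ICC 0, 0.05, 0.10 and 0.20. The Welch test showed the same inflation, so allowing for unequal variances alone does not cure it.

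**Step 3: reading the table.** The last two columns are alternatives. A test that ignores the groups still rejects at close to the planned rate under d = 0.44 (0.801, 0.795 and 0.783 at ICC 0.05, 0.10 and 0.20), but only because it runs above its nominal 5%. A small part of the power loss comes from the degrees of freedom: at ICC 0 the Satterthwaite calculation gives 0.799 against 0.803. The normal approximation, which omits that penalty, gives 0.785, 0.763 and 0.721 at ICC 0.05, 0.10 and 0.20.

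**Step 4: sample size that would restore 80%.** N = 3 × n(control), where n(control) = (1 + DE/2) × ((1.96 + 0.8416)/0.44)². For m = 4 to 5 this gives 192–195, 201–207 and 219–234 at ICC 0.05, 0.10 and 0.20. These are slightly low, because the same formula gives 183 rather than 186 at ICC 0.

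**The case against.** A reader might infer that the primary standard error *is* too small and that 80% power *is not* delivered. The article does not support that as fact. Both depend on a positive ICC that it does not give, and the primary outcome is a blinded rating of each parent–child pair, for which no within-group correlation is shown. With small clusters in one arm only, the loss is modest: about 2 to 3 points of power at ICC 0.05 or below. This objection stands, and it limits the severity.

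A reader might also infer that the plan has decided to analyse families as independent. It has not said so. Regression can carry a group term or clustered standard errors, and detailed model structure is commonly left to a statistical analysis plan, which is not shown. What can be said is narrower: the published analysis text does nothing about the grouping, and the robust standard errors it names serve another purpose. They would not address within-group correlation unless clustered on COS-P group.

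Finally, the word *independent* in the sample-size section could simply mean two unpaired arms, which is true of a parallel trial. Deleting the word would then fix nothing. But the point does not rest on the word, because the calculation reproduces only with no design effect.

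**Conclusion.** The point holds in conditional form. It is firm that 186 contains no allowance for group delivery in the COS-P arm and that the analysis section does not account for it. The consequence requires a positive within-group ICC: power then falls to about 0.79, 0.78, 0.75 and 0.71 at ICC 0.02, 0.05, 0.10 and 0.20, and an analysis ignoring the groups has type I error of about 5.3%, 5.7%, 6.4% and 7.8–8%.

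These figures assume 124 versus 62, mean group size 4.5, d = 0.44, a two-sided test, equal total variance and no attrition. If therapists lead several groups, the effective clusters are larger and the loss is greater; the article does not give the number of therapists. Severity is moderate rather than critical: the effect is small at ICC 0.05 or below and clear only from about 0.10. With positive ICC, the error from ignoring the groups makes the p-value for COS-P too small.

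**What to change.** 1. In *Sample size and power analysis*, replace the single power figure under independence with power over a stated ICC range, for example 0.78 at ICC 0.05 and 0.75 at 0.10, before attrition, and give the assumed group size.
2. Record the COS-P group ID of each intervention family. At the time of the article 64 participants had been randomised and recruitment was continuing, so this could be set up before analysis.
3. In *Analytical model*, state that the primary analysis and the other outcome analyses account for COS-P group. Either of two routes is acceptable: a partially nested mixed model with a random intercept for COS-P group in the intervention arm only and small-sample degrees of freedom (Satterthwaite or Kenward-Roger), or standard errors clustered on COS-P group with a small-sample correction.
4. Say how families without a group are handled. Randomisation is to an arm, stratified by site, and the article does not say when families are placed in groups. Since families may withdraw at any time, some intervention families may never join one. Treat them, like the controls, as singletons, so that the intention-to-treat set stays complete.

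The cost is a change of wording and one extra data field. The downside is slightly wider intervals and a slightly less favourable stated power. If the ICC is close to zero, almost nothing is lost.

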### Analytical model

For the intent to treat analysis of the primary, secondary and explorative outcomes, regression analysis and /or ANOVA will be used. For not normally distributed data, robust standard errors, truncation or transformation will be used. For missing data, the direct maximum likelihood method (full information likelihood) or multiple imputations will be used. In addition, per protocol analyses will be conducted for patients completing at least seven sessions, using regression analysis and /or ANOVA with robust standard errors, truncation or transformation when needed.

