### Hypothesis and aim of the study

We expect that an attachment based parenting intervention will benefit parents of children, who are referred to child psychiatric services and that the effect of the intervention also will extend to the child. We expect that the intervention will help parents to become more perceptive of the signals and needs of their child and improve parental sensitivity, parent-child relationship, children’s symptoms and parenting stress.

The aim of this trial is to investigate the effect of COS-P on maternal responsiveness and child psychiatric symptoms after the intervention and 6-months after the completion of COS-P. The primary objective is to investigate whether 10 weeks of COS-P have a positive effect on the observed sensitivity of mothers of children in the age range 3–8 years (age 2 years 11 months including), who are referred to psychiatric services with emotional and/or behavioral symptoms, all showing oppositional defiant symptoms.

The secondary objectives are to investigate whether COS-P has an effect on children’s psychiatric symptoms, children’s behavioral issues, maternal intrusiveness, parental coping with children’s negative emotions, parental reflective functioning and stress post-intervention and at 6 month follow-up.

An additional objective is to investigate possible moderators and predictors of treatment outcomes including parental attachment style, psychopathology, and depressive symptoms.

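### Robust standard errors are tied to non-normality, but with 2:1 allocation the condition that matters is unequal variance between arms

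*Protocol article*

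**What the plan says.** All statements are in the protocol article.

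- **Analytical model.** For the intention-to-treat analysis of primary, secondary and exploratory outcomes, "regression analysis and /or ANOVA will be used". The next sentence sets the exception: "For not normally distributed data, robust standard errors, truncation or transformation will be used". The per-protocol analysis repeats the same options, "with robust standard errors, truncation or transformation when needed", without defining the need. Missing data are to be handled by direct maximum likelihood or multiple imputation.
- **Randomization.** The arms are deliberately unequal: "participants are randomized 2:1 to the intervention group or control group in a web based randomization system".
- **Sample size and power analysis.** "124 participants in the intervention group and 62 in the control group are needed". The effect size of 0.44 is "for comparing the change in maternal sensitivity from baseline to follow-up between the intervention group and the control group".

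The article does not mention unequal variances between arms and gives no SD for either arm.

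**The concern.** The rule responds to the wrong feature of the data. With 186 families, a difference in means is approximately normal even if individual scores are not, so non-normality alone changes its standard error little. Unequal variance is different, because a larger sample does not remove its effect when the arms differ in size. The equal-variance standard error weights the arm variances by arm size. The true sampling variance of the difference weights them by the inverse of arm size. At 1:1 the two agree; at 2:1 they do not.

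Under the rule as written, an outcome that looks normal but has a different spread in the two arms stays with the default analysis. An outcome that looks non-normal may be truncated or transformed instead, and neither reliably equalises the variances.

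Unequal spread is plausible here. A treatment effect that varies between families generally changes the variance in the treated arm, and the article expects such variation: "An additional objective is to investigate possible moderators and predictors of treatment outcomes". COS-P alone is delivered in groups of 4–5 families, which can add variation in that arm. The primary outcome is built from ratings bounded at 1 and 5, so a rise could compress the COS-P arm. These mechanisms pull in different directions.

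At stake is the calibration of the primary p-value and confidence interval. They are too optimistic if the smaller TAU arm is the more variable, and too cautious if COS-P is.

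**Working it through.** **Inputs.** From the article: 124 COS-P and 62 TAU; d = 0.44; "Using significance level of 5% and power of 80%, and with a 2:1 randomization ratio". Assumed, because the article gives no figures: the ratio of arm SDs, shown as a range, and for step 4 the baseline–follow-up correlation and the strength of effect modification.

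**1. The plan's own figure.** TAU arm n = (1 + 1/2) × (1.960 + 0.842)² / 0.44² = 1.5 × 7.85 / 0.1936 = 60.8, so 61 TAU + 122 COS-P = 183, within 2% of 186. At 62 and 124, two-sided power is 0.803 (noncentral t) or 0.808 (normal). A one-sided test would need only 48 TAU families, so the plan is evidently two-sided. The sample size stands.

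**2. Standard errors.** With SDs s₁ (COS-P) and s₂ (TAU):

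- equal-variance: V_pooled = [(123 s₁² + 61 s₂²)/184] × (1/124 + 1/62)
- true: V_true = s₁²/124 + s₂²/62
- type I error = 2 × [1 − Φ(1.96 × √(V_pooled/V_true))]

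With n per arm at 1:1, both variances reduce to (s₁² + s₂²)/n, so the problem comes from the 2:1 ratio.

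Worked case, TAU/COS-P = 1.25 (s₁ = 0.8, s₂ = 1): V_pooled = (139.72/184) × 0.02419 = 0.01837; V_true = 0.00516 + 0.01613 = 0.02129. The SE ratio is √0.863 = 0.929, and 1.96 × 0.929 = 1.821 gives 6.9%.

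Worked case, TAU/COS-P = 0.80 (s₁ = 1.25, s₂ = 1): V_pooled = (253.19/184) × 0.02419 = 0.03329; V_true = 0.01260 + 0.01613 = 0.02873. The SE ratio is √1.159 = 1.076, and 1.96 × 1.076 = 2.110 gives 3.5%.

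**3. Range, with 200,000 simulated trials per row.**

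| SD ratio TAU/COS-P | pooled SE / true SE | type I, formula | type I, pooled (simulated) | type I, Welch (simulated) |
|---|---|---|---|---|
| 2.00 | 0.815 | 11.0% | 10.9% | 5.0% |
| 1.5 | 0.880 | 8.5% | 8.4% | 5.0% |
| 1.25 | 0.929 | 6.9% | 6.9% | 5.0% |
| 1.00 | 1.000 | 5.0% | 5.0% | 5.1% |
| 0.80 | 1.076 | 3.5% | 3.5% | 5.0% |
| 0.67 | 1.138 | 2.6% | 2.6% | 5.0% |
| 0.50 | 1.226 | 1.6% | 1.7% | 5.0% |

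Power at d = 0.44, taken on the root-mean-square of the two SDs, pooled against Welch: 0.802 v 0.800 at ratio 1; 0.793 v 0.832 at 0.80; 0.814 v 0.771 at 1.25. In the last case the pooled test's apparent advantage comes with its 6.9% error rate. If d is taken on the pooled SD instead, the figures at ratio 0.80 are 0.82 v 0.86.

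**4. What if COS-P helps the least sensitive mothers most?** Take baseline SD 1, correlation 0.5, and an effect that falls by b SD per baseline SD. Residual variance given baseline is 1 − 0.5² = 0.75.

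- *Change score.* TAU variance is 0.5² + 0.75 = 1. COS-P variance is (0.5 + b)² + 0.75, which is 1.24 at b = 0.2 and 1.75 at b = 0.5. The larger arm is the more variable: type I error 4.2% and 3.2%.
- *Baseline-adjusted regression, common slope.* COS-P residual variance is 0.75 + b²/9 and TAU 0.75 + 4b²/9. At b = 0.5 these are 0.778 and 0.861. Type I error is 5.1% (b = 0.2) and 5.4% (b = 0.5).
- *Unadjusted follow-up score.* COS-P variance is (0.5 − b)² + 0.75, that is 0.84 and 0.75, against 1 in TAU: type I error 5.7% and 6.2%.

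**The case against.** **Equal variance is not in the text.** True. The article says regression and/or ANOVA; a common residual variance is the ordinary meaning of those words, not a quotation. The article also does not say that the primary outcome will be treated as normal, and the maximum likelihood option has no stated variance structure. This limits how firmly the default can be attributed to the plan.

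**The variance estimator belongs in the statistical analysis plan.** Usually so, and an unseen plan may already deal with it. Naming robust standard errors for one situation does not forbid them in another. But the article is not silent here: it states a condition for using them, and that condition is the wrong one for unequal arms. The point concerns that stated rule.

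**The evidence for unequal spread is thin.** This stands in part. The moderator objective is only an intention to look. The larger gains in the worse-affected, reported in the COS-I part of the Introduction, come from an uncontrolled study of the longer programme and not from observed maternal sensitivity. The moderation by maternal attachment style in the COS-P part comes from a randomised trial, but concerns child attachment.

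**A stronger reading that the documents do not support.** A reader might infer that the primary test is anti-conservative because COS-P would lift the weakest mothers toward the rest and leave TAU the more variable arm. That describes follow-up scores. The sample size is set on change from baseline, and there the same mechanism widens the COS-P arm and makes the test conservative. With baseline adjustment the error nearly vanishes (step 4).

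**In the conservative direction the planned power survives.** This depends on the scaling: at ratio 0.80 the pooled test has 0.82 if d refers to the pooled SD and 0.793 if it refers to the root-mean-square SD. Either way the shortfall against 80% is negligible; the loss is relative to Welch.

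**Conclusion.** The point holds as a modest improvement to a stated rule. Non-normality is the wrong trigger in a 124 v 62 design, and the rule leaves normally distributed outcomes with unequal spread unprotected. For assumed SD ratios (TAU/COS-P) of 0.80 to 1.25, two-sided type I error runs from about 3.5% to 6.9%. Ratios further from 1 do more harm, but nothing in the article points to them. The direction is unknown.

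The conclusion rests on the ordinary reading of regression/ANOVA and on assumed SD ratios. The figures for effect modification rest also on an assumed correlation of 0.5. It does not show that the primary result will be wrong, and it does not touch the sample size.

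**What to change.** In the Analytical model section, and in the statistical analysis plan so that the two agree, remove normality as the condition. State that between-arm comparisons, primary outcome included, use heteroscedasticity-consistent standard errors (for example HC3) or Welch-type or arm-specific residual variances, whatever the distribution. HC3 suits least-squares regression; arm-specific residual variances suit the maximum likelihood route. Correlation within COS-P treatment groups is a separate matter that HC3 does not address.

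The cost is one sentence and one software option. If the variances are equal, the loss of power is about 0.2 to 0.3 percentage points (0.802 to 0.800 in the simulation above). The 186 families, the allocation ratio and trial conduct do not change. The Trial status section reports recruitment as ongoing with 64 participants randomised, so at that stage the change could be fixed before the between-arm analysis.
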